## Uncertainty, significance and multiplicity

All key estimates will be reported, including effect sizes and 95% confidence intervals, with significant figures aligned to the measurement precision. Statistical methods will be selected based on the scale of the outcome (continuous, ordinal, or dichotomous), and model performance metrics (AUC, calibration, Brier score, and decision-curve analysis) will be reported, along with confidence intervals obtained via resampling methods. Measurement-related uncertainty arising from electrode placement, skin preparation, and normalisation procedures will be mitigated through standardised acquisition protocols, predefined quality-control thresholds, and sensitivity analyses. Multiplicity is limited by prespecifying a single primary endpoint; secondary and exploratory analyses will be interpreted cautiously, with appropriate adjustment methods applied where necessary.

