## Sample size estimation

The sample size was estimated using the following formula:$$n={\left(Z\alpha /2\right)}^{2}\left(1-r^{2}\right)/d^{2}$$where Zα/2 (Confidence Interval) = 95%, CI = 1.96, r (Estimated Correlation value) = 0.6, and d (Precision) = 20%.

Considering the above values, *n* = 61

Thus, with a dropout rate of 20%. *n* = 76

Hence, the final sample size of this prospective cohort study was 76 participants with stroke.

The sample size determination is guided by a widely accepted rule of thumb for prediction modelling, which recommends approximately 10 outcome events per predictor parameter [27]. Based on this principle, the available sample size is expected to support the inclusion of a small and clinically meaningful set of predictors, anticipated to be around 7 (≈7 degrees of freedom) while minimizing the risk of overfitting. Consistent with guidance by Riley et al [28] we considered a target global shrinkage factor of ≥0.90 to limit overfitting and aimed for an anticipated discrimination performance (AUC) of approximately 0.75–0.80. Furthermore, the modelling strategy will incorporate penalised regression techniques and bootstrap-based internal validation to obtain optimism-corrected estimates of discrimination and calibration, consistent with TRIPOD recommendations.

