### Dependent variables (outcome)

Primary outcome measures, including FMA (upper and lower motor assessments), ARAT, and FAC, along with secondary outcome measures such as 10MWT, Mini BEST, and SIS, will be assessed at the 1st and 3rd months post-stroke. The primary endpoint of this study will be motor recovery measured by the FMA score at 3 months post-stroke. The outcome will be analysed on a continuous scale, with clinically meaningful thresholds explored secondarily for dichotomous interpretation where appropriate. In accordance with SRRR guidelines [9], endpoint timing in this study is aligned to biologically informed recovery windows. The additional assessment at the 1st month captures the early subacute phase, which is a critical time point for neural plasticity [[30], [31], [32]]. In contrast, the 3-month time point provides a pragmatic and biologically credible primary endpoint for clinical trials of stroke recovery, consistent with SRRR recommendations.

The FMA is the recommended outcome of upper (FMA-UE) and lower extremity (FMA-LE) motor function in people with stroke. It assesses voluntary movement, coordination, and reflex activity in 33 upper extremity and 17 lower extremity items scored on a scale between 0 and 2 [33].

The ARAT assesses the activity capacity of the upper extremity. It has 19 items ordered in four subscales with hierarchical scoring: grip (4 items), grasp (6 items), pinch (6 items), and gross movement (3 items). ARAT is sensitive to changes in motor recovery and is frequently used both in clinical practice and research to evaluate functional outcomes of the paretic arm [34].

The FAC is a 6-point (scored as 0–5) functional walking assessment of ambulation ability and independence in walking, determining the level of human support needed, regardless of whether assistive devices are used [35].

The 10MWTat a comfortable walking speed is a reliable method for the assessment of walking speed in people with stroke [36]. The 10 MWT will only be assessed in participants able to walk independently (FAC≥3).

The Mini BEST includes evaluation of anticipatory and reactive postural control, sensory orientation, and dynamic gait. It comprises 14 items and has a maximum score of 28 points. Each item will be scored from 0–2, where 0 indicates the lowest and 2 denotes the highest level of function [37].

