## Internal validation and model performance

Internal validation will be performed using bootstrap resampling to obtain optimism-corrected estimates of model performance. Model calibration will be evaluated by reporting the calibration intercept and calibration slope. Discrimination of the model will be assessed using the area under the receiver operating characteristic curve (AUC). Overall model performance will be quantified using the Brier score. The primary endpoint will be analysed as a (ΔFMA) as continuous outcome. Secondary analyses will explore clinically meaningful dichotomous thresholds for recovery based on published guidelines and expert consensus. Decision-curve analysis will be used to assess the net clinical benefit of the prediction model across a range of clinically relevant thresholds. In addition, repeated cross-validation using leave-one-out cross-validation (LOOCV) will be conducted as a sensitivity analysis to evaluate the robustness of model performance estimates.

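### Multiplicity is said to be limited by a single primary endpoint, but the endpoint as written is not single: no FMA score or form is fixed, and ARAT and FAC are also labelled primary

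*Protocol article*

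**What the plan says.** The section Uncertainty, significance and multiplicity gives one structural safeguard: "Multiplicity is limited by prespecifying a single primary endpoint". For everything else it adds that "secondary and exploratory analyses will be interpreted cautiously, with appropriate adjustment methods applied where necessary".

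Dependent variables (outcome) opens with a plural list: "Primary outcome measures, including FMA (upper and lower motor assessments), ARAT, and FAC". The same sentence sets these apart from the secondary measures (10MWT, Mini BEST and SIS) and schedules both groups at months 1 and 3. The next sentence designates one endpoint: "The primary endpoint of this study will be motor recovery measured by the FMA score at 3 months post-stroke". The scale is then described in two parts: "The FMA is the recommended outcome of upper (FMA-UE) and lower extremity (FMA-LE) motor function in people with stroke", with 33 upper and 17 lower extremity items.

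Table 1, under Measurement time points, gives FMA-UE and FMA-LE a row each and has no row for a total. Both are marked at months 1 and 3, and neither within 7 days.

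Internal validation and model performance gives another form of the endpoint: "The primary endpoint will be analysed as a (ΔFMA) as continuous outcome".

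**The concern.** A single prespecified endpoint limits multiplicity only if a reader can tell, before the data are seen, which number it is. Here the instrument (FMA) and the final visit (3 months) are fixed, but the score and the form are not. The choice of score can matter. Under Participants, eligibility may be met through the SAFE score or through knee extensor strength, so a participant may qualify on one limb only, and upper and lower extremity results may then differ.

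ARAT and FAC are also left without a place. They are called primary but are not the designated endpoint, and the rule on cautious interpretation and adjustment is written for secondary and exploratory analyses. At stake is mainly selective emphasis: after analysis, the best-performing of several models could be presented as the main result while the text assures readers that there was only one.

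**Working it through.** **1. What the plan's own figure rests on.** Sample size estimation uses n = z²(1 − r²)/d² with z = 1.96, r = 0.6 and d = 0.20. This gives 3.8416 × 0.64 / 0.04 = 61.5, stated as 61. With 20% dropout, 61 / 0.80 = 76.25, stated as 76. Both figures reproduce, and they are sized for one correlation at 95% confidence.

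**2. How many endpoints fit the text.**
- Score: FMA-UE, FMA-LE or total, so 3 readings. Table 1 favours two separate scores; no section chooses.
- Form: 3-month score (Dependent variables) or change (Internal validation), so 2 readings.
- Product: 3 × 2 = 6 versions of the primary endpoint. The reference visit for the change is a further open choice. Table 1 has no FMA before month 1, and Background variables names no baseline FMA.

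**3. How many outcomes carry the primary label.** By instrument there are three (FMA, ARAT, FAC). Counting FMA-UE and FMA-LE separately, as Table 1 does, there are four.

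**4. Illustrative size.** Assumptions, none of them in the plan: each outcome is tested once at an unadjusted two-sided 5%, all null hypotheses are true, and the test statistics share a common correlation ρ. The 5% level is borrowed from the 95% intervals the plan uses. For independent tests the chance of at least one false positive is 1 − 0.95^k. For correlated tests it was simulated with 1,000,000 multivariate normal draws.

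| Outcomes | ρ = 0 | ρ = 0.5 | ρ = 0.7 | ρ = 0.9 |
|---|---|---|---|---|
| 1 | 5.0% | – | – | – |
| 2 (FMA-UE, FMA-LE) | 1 − 0.95² = 9.75% | 9.1% | 8.3% | 7.0% |
| 4 (plus ARAT, FAC) | 1 − 0.95⁴ = 18.5% | 15.6% | 13.1% | 9.4% |

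**5. Cost of keeping two FMA endpoints.** Splitting 5% equally gives 2.5% each, so z = 2.241. With n = 61, the plan's formula solved for precision is d = z√((1 − r²)/n). This gives 1.96 × 0.8 / √61 = 0.201 at present and 2.241 × 0.8 / √61 = 0.230 after the split. Intervals become about 14% wider (2.241 / 1.96 = 1.143). To hold d at 0.20, n = 2.241² × 0.64 / 0.04 ≈ 80, or about 100 after 20% dropout (80 / 0.80).

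**The case against.** The strongest reply is that the text separates primary outcome measures, which are several, from the primary endpoint, which is one. Dependent variables names FMA at 3 months as that endpoint, and Internal validation again takes FMA as primary. On this reading ARAT or FAC could not properly be reported as the primary endpoint result. This stands in part: the multiplicity sentence has a basis. It does not settle which FMA score or form is meant, nor which rule governs ARAT and FAC.

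A reader might infer that the plan claims error control that does not exist, or that its false-positive rate is 18.5%. The documents support neither. The plan says multiplicity is limited, not controlled, and it states no test level, success rule or per-outcome test. The work is mainly prediction-model development by elastic net with bootstrap validation, reported through performance measures, effect sizes and 95% confidence intervals. The percentages above describe an assumed analysis.

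A reader might also infer that upper and lower extremity recovery will be modelled separately with different muscles. That is plausible from the aims, but no section states it.

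Finally, the choice of adjustment method is commonly left to an analysis plan that is not shown here. That is fair for the method. It does not excuse inconsistent statements about which outcome is primary, since these all stand in the article itself.

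**Conclusion.** The point holds as an inconsistency in how the primary endpoint is defined. The stated safeguard depends on one endpoint, but the text admits at least six versions of it and puts the primary label on three instruments, or four scores. ARAT and FAC have no stated multiplicity rule.

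Under an assumed unadjusted 5% test per outcome, the chance of at least one false positive is up to 9.75% for the two FMA scores (about 7% at correlation 0.9). For all four it is about 9% at correlation 0.9 and 18.5% at zero. These figures show scale only, because the documents give neither a test level nor any correlation between outcomes. In a prediction-model study the practical risk is selective emphasis on the best-performing outcome rather than a formal false claim. It should be corrected before analysis.

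**What to change.** In Dependent variables (outcome), name one FMA score (UE, LE or total), one time point and one form (3-month score, or change from a stated reference visit) as the sole primary endpoint. If change is chosen, Table 1 must show the reference assessment. Relabel ARAT, FAC and any FMA score not chosen as secondary, so that the existing rule for secondary analyses covers them. Align Internal validation and model performance and Uncertainty, significance and multiplicity with that definition. The cost is wording only, and the planned 76 need not change on this account, because it is already sized for a single correlation.

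If both FMA-UE and FMA-LE are to remain co-primary, remove the sentence about a single primary endpoint and state the adjustment. Holm is possible where p-values exist. Because elastic net does not routinely give p-values, correspondingly wider confidence intervals (97.5% for each score) fit the planned reporting better. The cost is some precision: intervals about 14% wider at the planned size, or about 80 participants before dropout to keep the planned precision.

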## Missing data

We will make every effort to ensure completeness of follow-up data at respective time points. In cases where data is missing, multiple imputation methods will be employed to facilitate comprehensive data analysis. Missing data in predictors and outcomes will be handled using multiple imputations by chained equations (MICE), under the assumption that data are missing at random. The imputation model will include all candidate predictors, outcome variables, and relevant auxiliary variables (such as age, baseline motor severity, stroke type, and time from stroke onset to assessment) to preserve observed associations. Twenty imputed datasets will be generated, and estimates will be pooled using Rubin’s rules.

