## Background

Stroke is a significant contributor to death and long-term disability worldwide [1]. Poststroke motor impairment is the most prevalent cause of adult disability, which has a major impact on healthcare worldwide [[2], [3], [4]]. Such impairments limit the capacity to carry out activities of daily living (ADL) [5], with >70% of stroke survivors experiencing hemiplegia affecting the upper or lower limbs, thereby affecting their functional independence [6]. According to International Classification of Functioning, Disability and Health (ICF) [7], motor functions encompass neuromusculoskeletal and movement-related functions, including muscle strength and endurance; voluntary movement control and coordination; and movement patterns related to walking, transfers, or upper body tasks [8].

Stroke recovery, in turn, refers to the extent to which functioning at different levels (body structure/function, activity capacity, and performance or participation) has returned to a prior stroke level [9]. Recovery is a multifaceted process that possibly combines spontaneous and learning-dependent processes, including restitution (repairing the impaired neural tissues), substitution (reorganizing partially impaired neural tissues to regain lost functions), and compensation (improving the gap between a patient's impaired skills and the demands of their environment) [10]. Even though recovery trajectories differ among individuals, several studies have suggested that recovery of body functions and activities is predictable even in the first days of stroke [10,11].

The capacity to estimate motor recovery would improve health resource use, individual-tailored rehabilitation programs, and patient and therapist expectations. Nevertheless, predicting motor function recovery remains a significant challenge owing to the high degree of variability among individuals, particularly when prediction relies solely on clinical evaluation [12]. While clinical assessment can serve as a strong independent predictor, particularly for patients with mild to moderate motor impairment [13], its predictive accuracy is more limited in those with severe deficits [13]. In such cases, adding neuroimaging and neurobiology biomarkers to prognostic models may help patients with severe motor impairments [[14], [15], [16]]. Unfortunately, the high expense, technical difficulty, and restricted accessibility of these methods in standard clinical practice limit their applicability [14].

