## Participants

We will include individuals aged 18–80 years, of any sex, with a first-ever ischemic or haemorrhagic stroke affecting the middle cerebral artery (MCA) or anterior cerebral artery (ACA). Recruitment will occur within seven days of stroke onset, and individuals reporting a Shoulder Abduction and Finger Extension (SAFE) score of <5(0–4) or knee extensor strength of <3/5 on the Medical Research Council (MRC) strength grade within this period will be included. Only those who are medically stable and able to follow simple commands will be included. The exclusion criteria will be individuals with a history of bilateral clinical strokes; those admitted more than seven days after stroke onset; patients who had undergone surgical interventions such as craniotomy or craniectomy; and individuals with pre-existing neurological or musculoskeletal disorders affecting motor functions.

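### The missing-data rule imputes every missing outcome under MAR without separating death, so taken literally it gives people who die before month 3 motor scores modelled on survivors

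*Protocol article*

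**What the plan says.** The Missing data section of the protocol article gives a general rule, "In cases where data is missing, multiple imputation methods will be employed to facilitate comprehensive data analysis", and then a specific one: "Missing data in predictors and outcomes will be handled using multiple imputations by chained equations (MICE), under the assumption that data are missing at random". It names the contents of the imputation model: all candidate predictors, the outcomes, and auxiliary variables such as age, baseline severity, stroke type and timing. It closes with "Twenty imputed datasets will be generated, and estimates will be pooled using Rubin’s rules". Vital status is not among the named variables, and no exception is made for participants who have died.

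The outcome being imputed is fixed in the section on dependent variables: "The primary endpoint of this study will be motor recovery measured by the FMA score at 3 months post-stroke". Table 1 places all outcome scales at months 1 and 3 only. The sample-size section allows for loss without splitting it by cause: "Thus, with a dropout rate of 20%. *n* = 76". The Bias section's measures against attrition are reminders and flexible scheduling.

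**The concern.** A Fugl-Meyer score that was not taken because the participant missed the visit exists and was not observed. A score for a participant who has died does not exist. MAR is an assumption about the first kind of gap and cannot justify filling the second. The imputation model learns the outcome from people who were assessed, so values generated for the dead are in effect survivors' values at the same predictor levels. A death before month 1 leaves no observed outcome at all, and both visits would be filled in.

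Death is foreseeable here. The cohort is recruited within a week of an ischaemic or haemorrhagic stroke with severe motor impairment, up to age 80. The Background itself says of the disease: "Stroke is a significant contributor to death and long-term disability worldwide".

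The article wants the model to guide rehabilitation intensity and goal setting, and judges it by calibration, Brier score and decision curves. These measures depend on absolute probabilities. If some outcomes counted as recovered belong to people who died, the probabilities are too favourable and the prediction no longer has a clear meaning.

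**Working it through.** **The plan's own figures.** Inputs from the sample-size section: z = 1.96, r = 0.6, d = 0.20, dropout 20%.

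- n = 1.96² × (1 − 0.6²) / 0.20² = 3.8416 × 0.64 / 0.04 = 61.5; the article states 61.
- 61 / (1 − 0.20) = 76.25; the article states 76.
- Planned losses: 76 × 0.20 = 15.2, about 15 people.

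The figures reproduce, and the point below does not alter them.

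**How many people would be affected.** The article gives no mortality m, so 5% to 20% is assumed. Deaths = 76 × m. Let 40% of survivors reach a good-recovery threshold (assumed) and let death be unrelated to the predictors. Imputation then reports 40% for the whole cohort, while the proportion alive and recovered is 0.40 × (1 − m).

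| Assumed m | Deaths among 76 | Recovered, deaths imputed | Alive and recovered | Gap (points) |
|---|---|---|---|---|
| 5% | 3.8 | 40% | 38% | 2 |
| 10% | 7.6 | 40% | 36% | 4 |
| 15% | 11.4 | 40% | 34% | 6 |
| 20% | 15.2 | 40% | 32% | 8 |

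**If death is commoner at low sEMG.** This was checked by simulation: 400,000 draws; correlation 0.6 between sEMG and outcome; good recovery set at the median, hence 50%; outcomes of the dead drawn from the survivors' regression on sEMG. For m = 5/10/15/20%:

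- Death unrelated to sEMG: alive and recovered 47.5/44.9/42.5/39.9%, against about 50% after imputation. The gap is about 2.5 to 10 points.
- Death commoner at low sEMG (assumed log-odds 0.7 per SD): 48.2/46.4/44.5/42.5%, against 50%. The gap is 1.8 to 7.5 points.
- Lowest sEMG quartile in the second case: 16.9/15.5/14.1/12.6%, against about 18.5%. The gap is about 1.6 to 5.9 points, smaller in points than overall but larger relative to the base.

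The gap equals m times the share of the dead imputed as recovered. In the second case at m = 20% that share is 37.5%, and 0.20 × 0.375 = 0.075, which agrees.

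**Discrimination.** AUC is 0.78 under either handling when death tracks sEMG. When death is unrelated to sEMG, it falls from 0.78 to 0.73 at m = 20% once death counts as not recovered.

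**The continuous model.** Values drawn from the survivors' own regression add no new information on its slope. The sEMG-FMA coefficients therefore stay close to a survivors-only fit.

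**The case against.** The strongest reply is that the article nowhere says deaths are treated as missing. The rule applies where data are missing, and a score that cannot exist is arguably not missing. A fuller protocol or analysis plan may say so. This stands to the extent that the defect follows from applying the rule literally and is not an announced intention. It does not dispose of the point. The article itself fixes the method, the assumption, the imputation model and the number of datasets, so a later document that left deaths out would be narrowing a published rule.

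The size is also open to challenge, and rightly. Entry requires medical stability and the ability to follow simple commands, and people who had a craniotomy or craniectomy are excluded. These criteria plausibly lower mortality. The 20% end leaves no room for any other kind of loss.

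Next, recovery among survivors and being alive and recovered are different targets, and the gap is bias only for the second. That is correct, but imputing the dead does not clearly serve the first target either. In the simulation with death commoner at low sEMG and m = 20%, the survivors' rate is 42.5 / 0.80 = 53%, the alive-and-recovered rate is 42.5%, and imputation gives 50%, which describes a cohort in which nobody dies.

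Finally, a survivors-only model still returns an expected score for someone who later dies. That stands, and is why deaths need reporting beside it.

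A reader might also infer that recurrent stroke, or neurosurgery after enrolment, goes unrecorded and distorts the outcome in the same way. The article does not support this. Its silence on event recording is normal in a condensed report, and Table 1 lists only the timing of predictors and outcomes. A survivor assessed after a recurrence has an observed score, which never reaches the imputation rule. Excluding such people would condition on an event unknown when the prediction is made.

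**Conclusion.** The point holds in a limited form. The missing-data rule does not separate death from missing data, and followed as written it creates motor scores for people who have died. On an assumed mortality of 5% to 20%, that is about 4 to 15 of 76 participants. The dichotomous analyses would overstate the chance of being alive and recovered by about 2 to 8 points if 40% of survivors recover. The true size depends on a death rate that the article does not give.

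The harm falls on calibration, Brier score and net benefit in analyses that the article calls secondary, and on what the prediction means. It would be wrong to infer that the continuous primary analysis is invalid or its coefficients seriously distorted. This is a correction to settle before the data are analysed, not a fundamental flaw.

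**What to change.** Amend the Missing data section so that MICE applies only to participants alive at the visit concerned. Record vital status at months 1 and 3 for everyone enrolled, including those who do not attend. State that the continuous FMA model predicts the score among 3-month survivors, and report the number of deaths alongside it. In the dichotomous analyses (AUC, calibration, Brier score, decision curve), count death as not recovered. Other estimands are defensible, but this one gives every participant a defined outcome and suits a probability of recovery; whichever is chosen should be stated.

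The cost is a few sentences and one vital-status field per visit. The sample size stays at 76, because 76 × 0.80 = 60.8 remain whatever the cause of loss. The downside is slightly fewer contributors to the continuous analysis and a slightly less favourable predicted chance of recovery.
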